# [name] et al. Trial Protocol

Effect of pre-emptive intervention on developmental outcomes for infants showing early signs of autism: A randomized clinical trial of outcomes to diagnosis

| Face-to-face assessment          |  |   |   |   |   |
|----------------------------------|--|---|---|---|---|
| AOSI                             |  | X | X |   |   |
| ADOS-2                           |  |   | X | X | X |
| PCI                              |  | X | X | X | X |
| MSEL                             |  | X | X | X | X |
| Clinical Best Estimate Diagnosis |  |   |   |   | X |

*Supplementary Table 3. Psychometric tests delivered at the baseline and follow-up assessments by a Research Assistant who is blind to the infant's group status.*

| Name                                                                                           | Details                                                                                                                                                                                                                                                                                                                                                                                                                                                                                                                                                                                                                                                                                                                                                                                                                                                                                                                                                                                                                                                      |
|------------------------------------------------------------------------------------------------|--------------------------------------------------------------------------------------------------------------------------------------------------------------------------------------------------------------------------------------------------------------------------------------------------------------------------------------------------------------------------------------------------------------------------------------------------------------------------------------------------------------------------------------------------------------------------------------------------------------------------------------------------------------------------------------------------------------------------------------------------------------------------------------------------------------------------------------------------------------------------------------------------------------------------------------------------------------------------------------------------------------------------------------------------------------|
| Autism Observation Scale for Infants (AOSI)                                       | 
Description: Semi-structured assessment developed specifically to elicit early behavioural risk factors of ASD in infants aged 6-18 months.
 
Procedure: Administered by researchers trained to protocol fidelity, and scored from videotape by researchers with demonstrated coding reliability (>80% agreement) who are blind to group allocation.
 
Scoring: Individual item scores (range 0-2) for 18 behaviours summed to produce AOSI Total Score (range 0-50; higher scores = more ASD symptoms).
 
Validity: Higher mean number of behavioural 'markers' at 12 and 18 months in infants with later ASD vs. no ASD; acceptable test-retest (<math>\geq .61</math>) and inter-rater reliability (<math>\geq .92</math>) for AOSI Total Score.
                                                                                                                                                                                                                        |
| Autism Diagnostic Observation Schedule – Second edition (ADOS-2): Toddler Module  | 
Description: Semi-structured assessment developed to elicit behaviours relevant to an ASD diagnosis in toddlers 12-30 months (Toddler Module) or aged 31 months and above (Module 1 and 2).
 
Procedure: Administered by researchers trained to protocol fidelity, and scored from videotape by researchers with demonstrated coding reliability (>80% agreement) who are blind to group allocation.
 
Scores: Continuous symptom measure: Total Algorithm Score (range 0-28; higher = more symptoms). Binary diagnostic classification: meets/does not meet established cut-off for ASD (i.e., non-verbal toddlers <math>\geq 12</math>; verbal <math>\geq 10</math>).
 
Validity: Continuous measure: Excellent test-retest and inter-rater agreement (Intra-class correlations <math>\geq .90</math>). Binary classification: Excellent sensitivity & specificity of cut-off scores for identifying ASD vs. other disabilities (<math>\geq .81</math>).
 |
| Parent Child Interaction (PCI)                                                                 | 
Description: Parent-infant free-play interaction sample. Filmed for 10mins, with standard set of age-appropriate toys provided.
 
Procedure: Footage coded by blinded trained researchers using Manchester-Assessment of Caregiver-Infant Interaction (MACI) procedures. Subset (10%) of footage scored by [name] for inter-rater reliability.
 
Scoring: Footage coded on 7-point Likert-type scales (higher scores = better quality interaction) for parent behaviour (sensitive responsiveness, non-directiveness), infant behaviour (affect, liveliness, attentiveness to parent), and dyadic interaction (engagement intensity, mutuality).
 
Validity: Low scores on MACI infant scales predict ASD diagnosis at 3 years.
                                                                                                                                                                                                                              |
| Mullen Scales                                                                                  | Description: Standardised developmental assessment norm-referenced 0 - 68                                                                                                                                                                                                                                                                                                                                                                                                                                                                                                                                                                                                                                                                                                                                                                                                                                                                                                                                                                             |

## [name] et al. Trial Protocol

Effect of pre-emptive intervention on developmental outcomes for infants showing early signs of autism: A randomized clinical trial of outcomes to diagnosis

|                                                                                                                  |                                                                                                                                                                                                                                                                                                                                                                                                                                                                                                                                                                                                                                                                                                                                                               |
|------------------------------------------------------------------------------------------------------------------|---------------------------------------------------------------------------------------------------------------------------------------------------------------------------------------------------------------------------------------------------------------------------------------------------------------------------------------------------------------------------------------------------------------------------------------------------------------------------------------------------------------------------------------------------------------------------------------------------------------------------------------------------------------------------------------------------------------------------------------------------------------|
| of Early Learning (MSEL)                                                                            | 
months.
 
Procedure: Trained, blinded assessors administer tasks directly with infants.
 
Scoring: Standardised t-scores (M = 50; SD = 10) and age equivalents computed for each sub-scale (higher scores = better developed skills).
 
Validity: Excellent test-retest and inter-scorer reliability for ages <math>\leq 24</math> months (<math>r \geq .82</math>). Infants at high risk of ASD score consistently poorly.
                                                                                                                                                                                                                                                           |
| Vineland Adaptive Behavior Scales – 2 nd edition (VABS-II)                               | 
Description: Caregiver-report measure of functional skills, norm-referenced 0 - 90 years. Communication and Socialization domains relevant to current trial.
 
Procedure: Parent completes form (i.e., not blind to group allocation) which is scored up by researcher according to manualised procedures.
 
Scoring: Domain Standard Scores (M = 100; SD = 15), and subdomain v-scores (M = 15; SD = 3) and age-equivalents computed (higher scores = better skills).
 
Validity: Excellent test-retest and inter-rater reliability for ages <math>\leq 24</math> months (<math>r \geq .81</math>). and evidence of low scores in ‘familial high risk’ infants.
 |
| MacArthur Communicative Development Inventory (MCDI)                                             | 
Description and Procedure: Caregiver-report checklists tallying Receptive and Expressive Vocabulary knowledge in infants aged 8-30 months. Words and Gestures (WG) form used at Baseline and F1 and Words and Sentences (WS) form used at Follow-up 2 and 3.
 
Scoring: Endorsed items summed to yield raw Receptive and Expressive vocabulary counts (possible range 0-680; higher score = more language skill).
 
Validity: Very strong internal consistency (<math>r \geq .95</math>).
                                                                                                                                                                                                    |
| Parenting Sense of Competence (PSOC)  and Depression Anxiety and Stress Scales (DASS)  | 
Description and Procedure: Caregiver-report questionnaires concerning sense of efficacy and stress in the parenting role: Completed at Baseline and the three Follow-up Assessments.
 
Scoring: Endorsed PSOC items summed to yield Satisfaction, Efficacy and Interest in being a Parent subscales, and for DASS items aggregate across domains of depression, anxiety and stress in the parent.
 
Validity: Shown to differentiate parents of infants at high-risk of ASD from low-risk controls
                                                                                                                                                                                                                      |
| Clinical Best Estimate Diagnosis                                                                                 | 
Description: Clinicians experienced in ASD diagnosis will review data collected and provide an appraisal of ASD diagnostic outcome, similar to previous trials.
                                                                                                                                                                                                                                                                                                                                                                                                                                                                                                                                                                    |

### 4.10 Criteria for termination of the trial

Discontinuation criteria for the trial reflect guidelines set out by the TGA. The trial will be terminated in the case that support for the trial is withdrawn from the HREC or sponsor. This includes the following possibilities:

- Evidence of significant deviation from the trial protocol that may threaten wellbeing of participants;
- Evidence that allowing the trial to continue carries an unacceptable risk of death, serious injury or illness to participants;
- Evidence that one treatment proves to be so much better or worse that to continue would disadvantage one group of participants;
- Evidence that conduct of the trial is in breach of the law.

## **[name] et al. Trial Protocol**

Effect of pre-emptive intervention on developmental outcomes for infants showing early signs of autism: A randomized clinical trial of outcomes to diagnosis

In regards to risk to participants, in the unlikely event of an SAE, a review would be conducted involving the SAC and the HREC board in relation to the future continuation of the trial. If the SAE is definitely due to trial participation, it may result in discontinuation of the whole trial (recruitment and treatment), depending on the decision made by the SAC and HREC based on available evidence concerning risk to participants. If the SAE is found to be possibly or probably due to trial participation, it will result in the affected participant/s immediately ceasing involvement in the trial. The SAC will then evaluate how the overall trial should proceed.

### **4.12 Identification of source data**

In this trial, the following documents will be considered source data:

- Hard copies of the following caregiver-report questionnaires:
  - Demographics Information
  - MCDI
  - VABS-II
  - PSOC
- Hard copies of the following protocols completed by Research Assistants or independent clinicians:
  - AOSI
  - ADOS-2
  - MSEL
  - Clinical best estimate diagnosis
- Hard copies of the following Research Therapist reports:
  - Fidelity rating scale
- Digital video footage of the following:
  - AOSI assessment
  - ADOS-2 assessment
  - PCI samples
  - In-home iBASIS-VIPP therapy sessions

## **8. SOURCE AND SELECTION OF PARTICIPANTS**

### **8.1 Source and feasibility of participant recruitment**

Infants will be recruited from two sources. At the WA site, staff at each of the 11 CDS ‘intake’ sites around the Perth metropolitan area will identify newly referred infants who may be eligible for the current study. The caregiver of any infant meeting the study criteria will be telephoned by a CDS staff member who will inform the families about the trial. The contact details of any consenting families will be sent immediately to the Research Assistant at the Telethon Kids Institute. The Research Assistant will then telephone the caregiver to conduct the eligibility screening, including verbal administration of the SACS-R^34 For those who express an interest in participating, an appointment will be made to attend the Telethon Kids Institute for a Baseline Assessment.

At the Melbourne site, potential infant participants will be identified through MCH nurses, who will perform developmental screens on infants at 12-months of age. Any infant who fails the

standard screen for developmental delay used by the nurses will be informed about this study. Caregivers interested in having their infant participate in the trial will have their contact details sent immediately to the Research Assistant at La Trobe University. The Research Assistant will then telephone the caregiver by telephone to conduct the eligibility screening, including verbal administration of the SACS-R. For those who express an interest in participating, an appointment will be made to attend La Trobe University for a Baseline Assessment.

## **5.2 Participant inclusion criteria**

Infants will be offered participation in this trial if they:

- (d) Are between 9 and 16 months of age;
- (e) Endorsement of three or more of the ‘key items’ on the 12-month old SACS-R^34 (absent/atypical pointing, waving, imitation, eye contact, response to name).
- (f) The primary caregiver involved in the trial speaks sufficient English to: (i) understand the requirements of the study, and (ii) is deemed to be able to participate fully in the therapy sessions.

## **5.4 Participant exclusion criteria**

Participants will be excluded from the study if they meet either of the following characteristics:

- (a) The infant has a diagnosed comorbidity (or significant clinical indicators of a comorbidity) known to affect neurological and developmental abilities (e.g., preterm birth < 32 weeks, cerebral palsy, Down syndrome, Rett syndrome, other chromosomal abnormality, hearing/visual impairment), and/or
- (b) The family does not intend to remain living in the Perth/Melbourne areas for the next two years.

## **5.4 Participant withdrawal criteria**

A premature discontinuation will occur when a participant for whom informed consent was obtained ceases participation in the study, regardless of circumstances, before the completion of the study. If a participant must be prematurely discontinued from the study, the primary reason for discontinuation must be recorded as one of the following:

- Failure to meet inclusion/exclusion criteria;
- The participant’s home is deemed by the Trial Coordinator to not provide a safe and healthy working environment for the Research Therapist.
- SAE linked to iBASIS-VIPP;
  - In the unlikely event that the participant’s psychological state deteriorates as a result of treatment they would be withdrawn from the study and alternative therapy or referral offered.
- Protocol deviation/violation, including lack of compliance;
- An infant participant received a diagnosis with a condition that meets ‘exclusion (a)’. In these cases, we will ensure that the participant has received an appropriate health and medical referral for their diagnosis (e.g., GP, paediatrician, audiologist etc.) at the time of their withdrawal from the study.
- Voluntary withdrawal of consent (reasons will be documented);
- Lost to follow-up (every effort will be made to contact the patient first; a certified letter will be sent).

## **[name] et al. Trial Protocol**

Effect of pre-emptive intervention on developmental outcomes for infants showing early signs of autism: A randomized clinical trial of outcomes to diagnosis

### *Data collection for withdrawn subjects:*

All enrolled participants who prematurely discontinue from the study regardless of cause will be asked to come in for a final evaluation. A final evaluation is defined as completion of the evaluations scheduled for the final post-treatment assessment (Follow-up assessment 3). Parents/caregivers refusing to have their infant assessed must be requested in writing to come in for a visit. A copy of the letter will be kept by the PI together with the source documentation. The reasons for premature discontinuation from the study will be reflected on the Study Termination Record of the CRF.

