## 4. TRIAL DESIGN

### 4.1 Primary and secondary outcomes

Infants will receive three follow-up assessments, time-locked to the baseline assessment:

4. *Follow-up assessment 1*: Immediately following treatment completion (6-months post-baseline), when infants are between 15 and 22 months of age (depending upon age at trial entry);
5. *Follow-up assessment 2*: Six-months following treatment completion (12-months post-baseline), when infants are between 21 and 28 months of age (depending upon age at trial entry).
6. *Follow-up assessment 3*: Eighteen-months following treatment completion (24-months post-baseline), when infants are between 33 and 40 months of age (depending upon age at trial entry).

The Primary Outcome measure is ASD symptom severity at immediate post-treatment outcome (first analysis phase) and ASD symptom severity across the three follow-up time points (second analysis phase). The Secondary Outcomes are developmental outcomes at immediate treatment end point (first analysis phase), and developmental outcomes across the three follow-up time points (second analysis phase).

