## **10. ASSESSMENT OF EFFICACY**

## 7.1 Specification of efficacy parameters and methods and timing for assessing and recording

Unless otherwise specified, all efficacy parameters will be recorded in source format. This will then be entered into an electronic database where it will be stored alongside participant's ID numbers. The database will be regularly checked for accuracy, and source documents will be retained to clarify any issues.

Autism Observation Scale for Infants will be used to measure the severity of autistic symptoms.  
*Method of Assessment:* Researcher-administered semi-structured play assessment with infant. Scored from video by researcher with demonstrated high level reliability, who is blind to treatment group.  
*Timing of assessment.* Baseline, Follow-up Assessment 1.

The Toddler Module of the Autism Diagnostic Observation Schedule – Second Edition will be used to measure the severity of autistic symptoms.

*Method of Assessment:* Researcher-administered semi-structured play assessment with toddler. Scored from video by researcher with demonstrated high level reliability, who is blind to treatment group.  
*Timing of assessment.* Follow-up Assessment 2 and 3.

The Manchester Assessment of Caregiver-Infant Interaction will be used to measure the quality of parent-infant interactions.

*Method of Assessment:* Parent-Infant free play interaction sample. Scored from video by researcher with demonstrated high level reliability, who is blind to treatment group.  
*Timing of assessment.* Baseline, Follow-up assessments 1, 2 and 3.

The Mullen Scales of Early Learning will be used to assess cognitive and motor ability.  
*Method of Assessment:* Researcher-administered standardised developmental assessment. Scored live by researcher administering the assessment.  
*Timing of assessment.* Baseline, Follow-up assessments 1, 2 and 3.

The Vineland Adaptive Behavior Scales – 2nd edition will be used to assess daily functional skills.

*Method of Assessment:* Caregiver-report questionnaire. Scored by researcher.  
*Timing of assessment.* Baseline, Follow-up assessments 1, 2 and 3.

The MacArthur-Bates Communicative Development Inventory will be used to assess early language development.

*Method of Assessment:* Caregiver-report questionnaire. Scored by researcher.  
*Timing of assessment.* Baseline, Follow-up assessments 1 (WG form), and 2 and 3 (WS form).

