### **10.5 The selection of participants to be included in the analyses**

Data will be analyzed through an ‘intention to treat’ approach and analyses will include all randomized participants.

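### Discontinued infants are asked only for the Follow-up 3 evaluations, and some discontinuation reasons arise only under iBASIS, so primary-outcome data can be lost unevenly by arm

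*Supplement*

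**What the plan says.** All references are to the final protocol (version 3) unless stated.

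- **Definition.** Section 5.4 (withdrawal criteria) says that a participant is discontinued when he or she "ceases participation in the study, regardless of circumstances, before the completion of the study". There is no category for stopping therapy while staying in follow-up. Section 4.10 adds that an infant with an SAE possibly or probably due to trial participation leaves the trial at once.
- **Reasons.** The list in section 5.4 includes an SAE linked to iBASIS-VIPP, a case where the "home is deemed by the Trial Coordinator to not provide a safe and healthy working environment for the Research Therapist", and "Protocol deviation/violation, including lack of compliance". It also includes failure to meet the entry criteria and a later diagnosis that meets exclusion (a).
- **Data then sought.** Under the heading on data collection for withdrawn subjects: "A final evaluation is defined as completion of the evaluations scheduled for the final post-treatment assessment (Follow-up assessment 3"). No time for this evaluation is given.
- **Primary outcome.** Section 4.1: "The Primary Outcome measure is ASD symptom severity at immediate post-treatment outcome (first analysis phase"). For phase 2, the same section takes severity over all three follow-ups as primary.
- **Analysis.** Section 10.5 takes an intention-to-treat "approach and analyses will include all randomized participants". Section 10.7 handles missing measures by maximum likelihood or multiple imputation, and says that these allow for selective but non-informative attrition. Discontinued infants are not replaced.

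**The concern.** An analysis of all randomised infants needs outcomes to be sought from all of them, including those who stop therapy. Here, stopping therapy for several listed reasons counts as leaving the study, and the one visit then requested is not the visit at which the phase 1 primary outcome is measured. Some of the reasons belong to one arm, and some relate to how therapy is going. Loss of that kind can make the arms differ for reasons other than the treatment effect. Later modelling can only partly recover outcomes that the protocol never tried to collect.

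**Working it through.** **1. Which reasons depend on arm?**

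| Reason (section 5.4) | Arm | Basis |
|---|---|---|
| SAE linked to iBASIS-VIPP | iBASIS only | By its wording |
| Home unsafe for the therapist | iBASIS only | Therapist home delivery is described only for iBASIS (section 4.7) |
| Lack of compliance | iBASIS in practice | Compliance monitoring is described only for iBASIS (section 6.3); other protocol deviations can occur in either arm |
| Ineligibility, exclusion (a) diagnosis, withdrawn consent, loss to follow-up | Either | No arm is specified |

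**2. What does the final evaluation supply?** Supplementary Table 2 places AOSI at baseline and Follow-up 1. Section 7.1 agrees: "Baseline, Follow-up Assessment 1". The Follow-up 3 evaluations contain ADOS-2 but no AOSI. For an infant who leaves before Follow-up 1:

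- Phase 1: no provision is made to collect the Follow-up 1 severity outcome.
- Phase 2: if the final evaluation is held at 24 months, one of the three time points is kept and up to two are lost. If it is held at withdrawal, the text does not say which time point it stands for.

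**3. The plan's own power figure.** The final protocol defers power to a separate analysis plan, which is not shown. The only power text is in section 9.1 of version 1: 85% power for 0.52 SD with 66 per group, two-sided alpha 0.05.

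- Normal approximation: 0.52 × √(66/2) = 2.987, and Φ(2.987 − 1.960) = 84.8%.
- Noncentral t: 84.3%.

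The figure reproduces, but it uses all 66 infants per group and makes no allowance for loss.

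**4. Illustrative size.** The documents give no dropout rate, so the inputs here are assumptions: a share m of iBASIS infants is lost, none is lost from Treatment as Usual, and those lost would have scored g SD worse than those kept.

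- Shift in an available-case contrast = m × g. With m = 0.10 and g = 0.5 to 1.0, this is 0.05 to 0.10 SD towards iBASIS.
- As a share of the 0.52 SD design effect: 0.05/0.52 = 10% and 0.10/0.52 = 19%.
- In AOSI points, with the version 1 SDs of change: 0.05 × 4.67 = 0.23 up to 0.10 × 6.98 = 0.70.
- Standard error in SD units, with 0.9 × 66 = 59.4 infants left in iBASIS: √(1/59.4 + 1/66) = 0.179.
- Two-sided type I error = 1 − Φ(1.96 − shift/SE) + Φ(−1.96 − shift/SE). A shift of 0.05 gives 5.9%, and a shift of 0.10 gives about 8.7%.
- Power for 0.52 SD falls from 84.3% to 82.2% with the same one-arm loss. Bias is therefore a larger issue than precision.

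**The case against.** The case on the other side has real force.

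- **The text does not cancel Follow-ups 1 and 2.** This is true. A reader might infer that the final evaluation replaces them, or that the primary outcome is lost for every discontinued infant. The documents support only that it can be lost, for infants who leave early. Still, once participation has ceased, no other visit is requested.
- **The battery is not plainly unsuitable for a young infant.** A reader might infer that evaluations meant for 33 to 40 months do not fit an infant of 12 to 19 months. Supplementary Table 3 does not bear this out: the ADOS-2 Toddler Module covers 12 to 30 months, MSEL 0 to 68 months, VABS-II 0 to 90 years and MCDI 8 to 30 months. Only the best-estimate diagnosis is plainly tied to the later age.
- **AOSI may not be the only severity measure at Follow-up 1.** Table 2 also marks ADOS-2 there, whereas section 7.1 times it at Follow-ups 2 and 3, and section 4.1 names no instrument. This does not close the gap, because no Follow-up 1 visit is requested after discontinuation.
- **Comorbidity detection.** It is tempting to argue that home visits make an excluding diagnosis likelier to be noticed under iBASIS. No text supports this, and Treatment as Usual may include referral to a developmental paediatrician (section 9.1, treatment schedule).
- **Ineligibility may be found before allocation.** Discontinuation counts from consent, which precedes randomisation. Only cases found after randomisation matter here.
- **The planned analysis is not an available-case contrast.** Maximum likelihood or multiple imputation with arm in the model handles loss that depends on arm and on observed data. What stands is the remainder: loss tied to unobserved outcome. The separate analysis plan may hold sensitivity analyses, so none is said to be missing.
- **Numbers may be small.** The protocol expects very few adverse events. Non-compliance and unsafe homes are not covered by that expectation.

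**Conclusion.** The point holds as a gap in the data-collection rule and should be fixed. Discontinuation means leaving the study, only the Follow-up 3 evaluations are then sought, and two reasons, plus compliance in practice, belong to the iBASIS arm. Primary-outcome data can therefore be lost selectively by arm, and possibly in relation to outcome. Loss through treatment-related deterioration or non-compliance puts the non-informative assumption of section 10.7 in doubt.

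The size is unknown. The shift of 0.05 to 0.10 SD and the type I error of about 6% to 9% rest on an assumed 10% loss in one arm, an assumed 0.5 to 1.0 SD worse outcome, and an available-case contrast. The planned methods would remove the part that observed data explain.

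A reader might conclude that the intention-to-treat analysis cannot be carried out. The documents do not support that: all randomised infants can still enter the model, but for those lost early the result leans on an untestable assumption that more complete follow-up would largely avoid.

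**What to change.** - In section 5.4, separate stopping therapy from withdrawing consent for follow-up.
- Replace the final-evaluation sentence. Every randomised infant whose family still consents to follow-up is sought for Follow-ups 1, 2 and 3, at the times counted from baseline and with each visit's own battery, and stays in the analysis. This includes infants found ineligible, or given an exclusion (a) diagnosis, after randomisation.
- Reconcile sections 4.10 and 5.4 with the withdrawn-subjects text and section 10.5, stating whether leaving the trial also ends outcome assessment. No criterion for stopping therapy needs to change for this.

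The cost is some protocol wording and a small number of extra retained visits, all of which are already in the assessment schedule.
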